### Data management

Data will be collected by researcher 3 directly from the child or adolescent and their parent/guardian. Data will be handled confidentially, and patients will be anonymized. The collected information will be kept for 5 years in accordance with the rules of the Committee of Universidade Federal do Rio Grande do Norte.

All participant data will be recorded in Excel files by researcher 1. All data will be checked by the researcher 1 and rechecked by researcher 2, neither of whom participate in the study’s data collection phase, which ensures the reliability of the data.

### Statistical analysis

Intention-to-treat analysis will be employed to prevent overestimation of intervention efficacy. The numerical data will be presented in averages, while the categorical data will be presented in a frequency distribution. Once data collection is complete, the data distribution normality will be verified by the Shapiro-Wilk test.

Fisher’s Exact Test will be used for intragroup analysis of categorical data, while the two-way mixed-design analysis of variance (ANOVA) test (a repetition factor and a group factor), followed by the Bonferroni post hoc test, will be applied to the numerical data. The effect size (ES) will be analyzed using Cohen’s *f*. If data are non-parametric, the Friedman test with Dunn’s post hoc test will be used for intragroup analysis. The ES will be analyzed using Kendall’s *w*. The Mann-Whitney test will be applied for intergroup analysis, and the ES will be analyzed using Cohen’s *r*. Each ES will interpreted on the basis of Cohen as follows: small (0.21–0.49), medium (0.50–0.79), or large (≥0.80) [54].

All the analyses will consider a confidence interval of 95% (CI95%) and a statistical significance of *P* < 0.05. The Statistical Package for Social Science (SPSS) 20.0 (IBM Corp., Armonk, United States) will be used to analyze the data.

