**Methods:**

This study will be a two-arm, prospectively registered, randomized controlled trial with blind assessors and twenty 6- to 18-year-old individuals with cystic fibrosis (CF) from two different Brazilian states. People with CF will be randomly allocated to either the experimental or control group using block randomization, stratified by puberty stage,. Participants from both groups will receive an educational intervention and will be asked to continue their usual daily treatment for the full duration of the study. Those in the experimental group will perform AIT on a cycle ergometer at home three times a week, for 8 consecutive weeks. The sample characterization will include an assessment of puberty stage, socioeconomic status, dyspnea, and anthropometry. The primary outcome will be the change in glucose tolerance, while the secondary outcomes will include lung function, exercise tolerance, respiratory muscle strength, quality of life, and CF exacerbations. All outcomes will be assessed at baseline, week 9, and week 17.

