#### CF exacerbations

In order to evaluate CF exacerbations, which normally require an increase and/or modification of antibiotics, the following Fuchs criteria adapted by the European Consensus Group will be used [32]: change in volume and/or color of secretion; increases in coughing, fatigue or lethargy; anorexia or weight loss; decrease in lung function of 10% or more as observed on X-ray; and increased dyspnea. The individual must present at least two of these criteria for an exacerbation to be confirmed.

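### Fisher's exact test is assigned to within-arm categorical data, where it does not test change, and no between-arm test is named for categorical outcomes such as CF exacerbation

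*Protocol article*

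**What the plan says.** The Statistical analysis section of the protocol article deals with categorical and numerical data separately.

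- Categorical data, presentation: "the categorical data will be presented in a frequency distribution".
- Categorical data, test: Fisher's method is the only one named, and its role is given as "Exact Test will be used for intragroup analysis of categorical data".
- Numerical data: a two-way mixed ANOVA with a repeated factor and a group factor, "followed by the Bonferroni post hoc test, will be applied to the numerical data".
- Non-parametric fallback within arms: "If data are non-parametric, the Friedman test with Dunn’s post hoc test will be used for intragroup analysis".
- Non-parametric fallback between arms: "The Mann-Whitney test will be applied for intergroup analysis".

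CF exacerbation is a declared outcome. In the abstract's Methods, "the secondary outcomes will include lung function, exercise tolerance, respiratory muscle strength, quality of life, and CF exacerbations". The CF exacerbations section gives a rule that each child either meets or does not: "The individual must present at least two of these criteria for an exacerbation to be confirmed". The abstract and the Intervention section set three assessments: baseline, week 9 and week 17.

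**The concern.** Within one arm, the repeated categorical observations come from the same children. Fisher's exact test assumes independent observations, so it is not a test of within-child change. The paragraph uses *intragroup* and *intergroup* as separate terms, and it gives categorical data only the first.

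At stake is a declared secondary outcome. The Background hypothesises that the training will improve every outcome. For exacerbation, an analyst who follows the text literally would report a within-arm p-value from an unsuitable test and no contrast between the randomised arms. That p-value could be significant when no child changed, or far from significant when most did.

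**Working it through.** **Inputs.** 10 children per arm (Sample size calculation); paired visits (abstract, Intervention); a yes/no exacerbation rule (CF exacerbations). The document gives no exacerbation rates or within-child correlations, so those used below are assumptions.

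**The plan's own figure.** The plan gives no number for this point. Its total of 20 can be reproduced as a repeated-measures ANOVA interaction with f = 0.30, two groups and three visits, assuming correlation 0.5 and sphericity. Noncentrality = f² × N × m / (1 − ρ) = 0.09 × 20 × 3 / 0.5 = 10.8 on 2 and 36 degrees of freedom, and power is 81.2%. The choice of categorical test does not enter this calculation; it only supplies n = 10 per arm.

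**Use A: Fisher on the first-visit by second-visit cross-table.**

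1. Five children positive at both visits, five negative at both, no changers. The table is [5, 0; 0, 5]. Each of the two extreme tables has probability 1/C(10,5) = 1/252, so Fisher p = 2/252 = 0.008. Exact McNemar has no discordant pairs, so p = 1.
2. A fall from 8/10 to 2/10, with six changers all in one direction. The table is [2, 6; 0, 2]. Its probability is C(8,2) × C(2,0) / C(10,2) = 28/45 = 0.62, the most probable table, so Fisher p = 1.0. Exact McNemar p = 2 × 0.5⁶ = 0.031.
3. Rejection rate at the 0.05 level when the true prevalence does not change. With prevalence p and within-child correlation ρ, set p11 = p² + ρp(1 − p), p10 = p01 = p − p11 and p00 = 1 − p11 − 2 × p10, then enumerate all tables for n = 10. Fisher on the cross-table rejects as follows:
   - ρ = 0.5: 17% (p = 0.3) and 21% (p = 0.5)
   - ρ = 0.8: 53% (p = 0.3) and 66% (p = 0.5)

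**Use B: visits stacked as if they were independent groups.**

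4. A fall from 6/10 to 0/10. Fisher p = 2 × C(10,6) × C(10,0) / C(20,6) = 2 × 210 / 38,760 = 0.011. Exact McNemar on six one-way changers gives 0.031.
5. With no true change and ρ = 0.5, the actual size is 0.0007 (p = 0.3) to 0.0008 (p = 0.5). Here the test is conservative, not inflated, but it still ignores the pairing.

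**Between arms, where Fisher is valid.** At 10 v 10, 0 v 5 events gives p = 2 × C(10,5) / C(20,5) = 2 × 252 / 15,504 = 0.033, and 1 v 6 events gives p = 0.057. Exact power is 13% for true rates of 50% v 20% and 47% for 60% v 10%.

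**The case against.** The strongest reply is that *intragroup* is a slip for *intergroup*. Fisher's test is a standard between-arm test in small samples, so this is plausible. It would make the test right for the arm comparison and leave only a within-arm test unnamed. But the sentence would still say the wrong thing, and an analyst should not have to guess.

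A second reply is that exacerbations may be counted per child, in which case the ANOVA or Mann-Whitney would apply. The article states no count and gives only the yes/no rule, so the consequence for exacerbation is conditional on a yes/no analysis.

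A third is that a fuller analysis plan may settle this. A fuller plan can add detail, but here the article names a test for a setting that does not suit it. A plan that followed the article would carry the error forward, and one that departed from it would contradict it.

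The size of the error also depends on the layout. The false signal of change arises in the cross-table use; the stacked use is conservative. The fix would not bring much power with 10 per arm.

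A reader might infer three stronger points, which the document does not support:

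- *That the primary outcome loses its arm comparison, or that glucose-tolerance class is a lost endpoint.* The Primary outcome section gives diagnostic thresholds but does not declare class an analysed endpoint. The OGTT glucose and insulin values are numerical and are compared between arms.
- *That the non-parametric branch rests on within-arm tests because Friedman's "post hoc test will be used for intragroup analysis".* The same paragraph supplies Mann-Whitney between arms, and the ANOVA has a group factor. Nothing says that conclusions will be drawn by contrasting one arm's p-value with the other's.
- *That the authors intend never to compare categorical outcomes between arms.* That follows only from reading the sentence literally; the article does not say so.

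**Conclusion.** The concern holds in a limited form. The stated rule is wrong on either reading: it is an unsuitable test for paired data, or it carries the wrong label for a between-arm test. Read literally, it leaves CF exacerbation, analysed yes/no, without a randomised comparison.

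The size is shown by example. At n = 10, Fisher on the cross-table gives p = 0.008 where nobody changed and p = 1.0 where McNemar gives 0.031. It rejects in 17–66% of cases with no true change, for assumed prevalences of 0.3–0.5 and correlations of 0.5–0.8. These rates apply to the cross-table use only.

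The numerical OGTT outcome and the sample size are untouched. This is a correction to make before analysis, of moderate to low severity, and it does not threaten the trial's main question.

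**What to change.** Replace the Fisher clause in the Statistical analysis section with text to this effect: Fisher's exact test compares the two arms for categorical outcomes (CF exacerbation as yes/no per child, and glucose-tolerance class only if it is analysed). For a yes/no outcome the result is reported as a risk difference with a 95% CI. Any within-arm change in a yes/no variable uses exact McNemar for two visits or Cochran's Q for three, and is descriptive.

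If exacerbations are to be counted rather than scored yes/no, say so and name the between-arm test for the count.

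The cost is one or two sentences, with no new data and no change in sample size. With 10 children per arm, the interval will be more informative than the p-value.

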### Sample size calculation

The sample size calculation was performed by GPower 3.1 software, with a power of 80% and an α of 0.05 being adopted. This procedure was based on the study by Beaudoin et al. (2017) [21], which presents a similar design regarding the same number of groups and the use of exercise as an intervention, although it was developed for adults with CF. In this study, the variable area under the glucose curve after the concurrent exercise program presented values of 34.47 ± 4.23 in the experimental group (EG) and 40.20 ± 11.96 in the control group (CG), with an effect size of 0.30. Based on these parameters, the sample size calculation was 20 participants, with 10 in each group.

The children and the adolescents who discontinue participation in the study will be invited to participate in the assessments 8 weeks after starting treatment, as well as 8 weeks after the end of the intervention. Thus, all individuals will be included in the intention-to-treat analysis.

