### Randomization and allocation

Assignment of study participants to the intervention groups will be performed using block randomization [34], with stratification by puberty stage (prepuberty or puberty) [35, 36] being accomplished with the randomization platform found at www.sealedenvelope.com. Participant allocation will be concealed in sequentially numbered and sealed opaque envelopes prepared prior to the study by a research assistant, who will not be involved in the study.

Researcher 1 will be responsible for allocation concealment, researcher 2 will randomize, researcher 3 will conduct an evaluation of the sample while blinded to the groups, researcher 4 will apply the training protocol, and researcher 5 will analyze the data.

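### The two-factor mixed ANOVA gives no baseline-adjusted treatment difference, leaves out the puberty stratum, and cannot by itself deliver an analysis that includes everyone

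*Protocol article*

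**What the plan says.** Protocol article, Statistical analysis: numerical data are to be analysed with "the two-way mixed-design analysis of variance (ANOVA) test (a repetition factor and a group factor", followed by Bonferroni post hoc tests. If the data are not normal, the Friedman test is used within groups and the Mann-Whitney test between groups. No covariate or stratum term is named for any of these.

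Abstract, Methods: "All outcomes will be assessed at baseline, week 9, and week 17". The Intervention section repeats this schedule, so the repetition factor has three levels and the first of them precedes treatment.

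Randomization and allocation: blocks are used "with stratification by puberty stage (prepuberty or puberty").

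Sample size calculation: participants who discontinue will be invited to both later assessments, from which the section concludes that "all individuals will be included in the intention-to-treat analysis". The design figure is "the sample size calculation was 20 participants, with 10 in each group", "with a power of 80% and an α of 0.05 being adopted", "with an effect size of 0.30".

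**The concern.** Three features of the named model do not fit the design around it.

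- **Baseline as an outcome level.** The main effect of group averages in a visit at which no treatment effect can exist. The interaction asks whether the two profiles differ in any way over three visits, so it does not estimate the difference at a chosen visit adjusted for baseline.
- **Stratum left out.** The investigators thought puberty stage important enough to stratify on, yet neither the ANOVA nor its rank-based fallback uses it.
- **Who is analysed.** An invitation does not secure attendance. A classical mixed ANOVA and the Friedman test both need every visit, and no method that keeps incomplete cases is named beside the promise to include everyone.

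With 20 participants, modest losses of precision or of people matter. A drift towards a completers' analysis would also weaken the intention-to-treat claim that the Discussion lists among the trial's strengths.

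**Working it through.** **1. The plan's own figure.** The article names neither the test nor the correlation. I assume Cohen's f = 0.30, 2 groups, correlation ρ = 0.5, sphericity, and a within-between interaction with m visits:

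λ = f²·N·m/(1 − ρ), df = (m − 1) and (N − 2)(m − 1).

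- m = 3, N = 20: λ = 0.09 × 20 × 3/0.5 = 10.8 on 2 and 36 df; power 81.2%. N = 20 is reproduced.
- m = 2, N = 20: λ = 7.2 on 1 and 18 df; power 71.8%. Not reproduced (N = 24 would be needed).
- A between-group factor with three visits would need N = 62.

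This supports reading the planned treatment test as the interaction, with baseline as one of three levels.

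**2. Effect scale.** The source values are "34.47 ± 4.23 in the experimental group (EG) and 40.20 ± 11.96 in the control group (CG"). Pooled SD = √[(4.23² + 11.96²)/2] = 8.97, so d = 5.73/8.97 = 0.639 and d² = 0.408.

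**3. Baseline as a level.** Assume 10 per arm, compound symmetry and a sustained effect, so the arm differences over the visits are (0, d, d).

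- *Main effect:* the averaged difference is (0 + d + d)/3 = 2d/3 = 0.426, one third lower than d. The variance of a three-visit mean is (1 + 2ρ)/3 = 0.667. λ = 5 × 0.426²/0.667 = 1.36 on 1 and 18 df; power 20%.
- *Interaction:* the centred differences are −2d/3, d/3, d/3, with sum of squares 2d²/3 = 0.272. λ = 5 × 0.272/0.5 = 2.72 on 2 and 36 df; power 27%.
- *Week 9 ANCOVA on baseline:* residual variance is 1 − ρ² = 0.75. λ = 5 × 0.408/0.75 = 2.72 on 1 and 17 df; power 34% before chance baseline imbalance is allowed for, and about 32% by simulation.

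At ρ = 0.5 the last two have the same λ. The ANCOVA gains only because it spends 1 numerator degree of freedom instead of 2. The gain shrinks as ρ rises:

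| ρ (assumed) | Interaction | Week 9 ANCOVA |
|---|---|---|
| 0.5 | 27% | 32% |
| 0.7 | 43% | 45% |
| 0.8 | 60% | 59% |

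**4. Puberty stratum.** Simulation with two strata of 10, balanced by arm, ρ = 0.5.

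- If puberty shifts all three visits equally, the shift cancels from the interaction, whose true size stays at about 5%.
- If puberty also shifts the post-baseline values by 0.8 SD (assumed), the interaction has a true size of about 3.7%. Its power at d = 0.64 is 23%, against 33% for a week 9 ANCOVA with baseline and puberty. An ANCOVA on baseline alone has 22.5%, so here the gain comes from the stratum term.

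**5. Incomplete participants.** Assume 10% missing at each follow-up visit.

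- Independent misses: 20 × 0.9² = 16.2 complete. Step 1 with N = 16: λ = 8.64 on 2 and 28 df; power 70%. The chance that all 20 are complete is 0.81²⁰ = 1.5%.
- Same people miss both visits: 20 × 0.9 = 18 complete. λ = 9.72 on 2 and 32 df; power 76%.

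**The case against.** The strongest reply is that the planned test is sound and the losses are small. Much of this stands.

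- A reader might infer that the ANOVA is biased or invalid because baseline is a level. It is not: the group-by-time interaction compares changes between randomised arms. It loses little to ANCOVA at ρ = 0.5 and nothing at 0.8, and the documents give no correlation. The diluted main effect matters only if it is read as the treatment test, which the sample size reconstruction does not suggest.
- Bonferroni post hoc tests and 95% confidence intervals are planned and can address single visits. They would still be unadjusted for baseline and stratum, and no visit is named as primary.
- A reader might take the loss that omitting a stratum causes in a plain one-visit comparison and apply it to the planned test. That does not carry over: a puberty effect constant over time cancels from the interaction. Where puberty does affect change, the test becomes conservative, so false positives do not increase.
- A reader might infer that the plan states a rule dropping anyone with a missed visit. It states no such rule. The loss follows from how a classical mixed ANOVA and the Friedman test work, and a fuller plan that is not shown could add imputation or fit the same two factors as a mixed model. What remains is the mismatch within the article: inclusion of everyone is stated as a consequence of an invitation, and no named method secures it.

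**Conclusion.** The point holds as a recommendation to improve a stated method and to correct an over-firm sentence. It does not show that the analysis is invalid. The named model gives a 2-df omnibus test where one adjusted difference is wanted, and it ignores a stratum already collected.

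The size depends on assumptions outside the documents. Baseline adjustment adds about 5 percentage points of power at ρ = 0.5 and none near 0.8. Stratum adjustment adds about 10 points if puberty shifts post-baseline values by 0.8 SD, and very little if its effect is constant. Loss of incomplete cases takes the reconstructed design power from 81% to 70–76% at 10% missing per visit.

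The change should not be expected to rescue power: at d = 0.64 no option in the table exceeds about 60%.

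**What to change.** Analyse the week 9 and week 17 values with a linear mixed model in the same SPSS. Use fixed effects for arm, visit, arm-by-visit, baseline value and puberty stratum, and all available follow-up data. Report the adjusted arm difference with its 95% confidence interval at each visit. The investigators should fix the primary visit in advance; week 9, the end of training, is one candidate, but the documents do not rank the visits. Report how many participants contribute at each visit.

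Reword the intention-to-treat sentence to say that participants with at least one follow-up value are analysed as randomised under a missing-at-random assumption. Those with baseline only add nothing to the treatment estimate in this model, so the new model does not make the present sentence true either.

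The cost is wording, with no new data or software, and two error degrees of freedom for baseline and stratum.

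### A Shapiro-Wilk result decides whether the primary comparison has a group-by-time test; the fallback has none and does not fix what its Mann-Whitney test compares

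*Protocol article*

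**What the plan says.** The abstract defines the primary endpoint as a change, measured at three times: "The primary outcome will be the change in glucose tolerance" and "All outcomes will be assessed at baseline, week 9, and week 17".

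The Statistical analysis section then sets out:

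- **The switch:** "Once data collection is complete, the data distribution normality will be verified by the Shapiro-Wilk test". It does not say which values are tested (arms pooled or separate, each visit, changes, or residuals).
- **The main analysis:** a two-way mixed-design "ANOVA) test (a repetition factor and a group factor), followed by the Bonferroni post hoc test, will be applied to the numerical data". This design carries a group-by-time term, which asks whether change differs between arms.
- **The fallback within arms:** "If data are non-parametric, the Friedman test with Dunn’s post hoc test will be used for intragroup analysis".
- **The fallback between arms:** "The Mann-Whitney test will be applied for intergroup analysis". No variable, visit or baseline adjustment is named.

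The Sample size calculation section gives 20 participants, 10 per arm, at 80% power, α 0.05 and an effect size of 0.30. It cites post-programme glucose AUC of 34.47 ± 4.23 against 40.20 ± 11.96. Randomization is stratified by puberty stage.

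**The concern.** A fallback for non-normal data should answer the same question with weaker assumptions. This one does not clearly do so. The mixed ANOVA compares the course over time between arms. The fallback splits that into a within-arm question (Friedman) and a between-arm question (Mann-Whitney), and neither contains the group-by-time term.

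Three things are at stake:

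- Which analysis is primary depends on a test with little power at this sample size.
- The only fallback procedure that explicitly uses all the visits never compares the arms. A result that is significant with training and not significant in control is easily misread as an effect.
- The one between-arm test can be run on raw values or on change, at week 9 or week 17. That is 2 × 2 = 4 versions of the primary result, with no stated choice among them.

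**Working it through.** **1. The article's own sample size.** Pooled SD = √[(4.23² + 11.96²)/2] = √[(17.89 + 143.04)/2] = 8.97. Then d = (40.20 − 34.47)/8.97 = 0.64 and d/2 = 0.32, close to the stated 0.30 if that is Cohen's f (the metric is not named).

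For a repeated-measures ANOVA, within-between interaction, f = 0.30, 2 groups, 3 visits and assumed correlation ρ = 0.5:

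- λ = f²·N·m/(1 − ρ) = 0.09 × 20 × 3/0.5 = 10.8
- degrees of freedom (2 − 1)(3 − 1) = 2 and (20 − 2)(3 − 1) = 36
- power = 0.81, and N = 20 is the smallest even total that reaches 80%

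So 20 is reproduced by a repeated-measures model at three visits. The within-factor variant gives the same N, so the interaction reading is likely but not proven. The between-factor variant at the same settings needs 62. On the interaction reading, the size rests on the term that the fallback drops.

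**2. The switch.** In simulation with n = 10, Shapiro-Wilk detects log-normal skew (σ = 0.5, an assumed shape) in only about 24% to 26% of samples. If it were applied to each of six arm-by-visit cells of truly normal data, at least one would reject in about 1 − 0.95⁶ = 26%. That figure treats the cells as independent, and the six-cell scheme is an assumption.

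**3. Friedman within arms.** Suppose both arms have the same true shift from baseline at both later visits, so there is no treatment effect. With 10 per arm, if each arm is significant with probability p, exactly one arm is significant with probability 2p(1 − p), which cannot exceed 50%. Simulated at ρ = 0.5:

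| Common shift (SD) | Exactly one arm significant | Training arm only |
|---|---|---|
| 0.3 | 18% | 9% |
| 0.5 | 36% | 18% |
| 0.6 | 43–44% | 22–23% |
| 0.7 | 51% | 26% |
| 1.0 | 42% | 21% |

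The 51% is the 50% ceiling plus simulation error (2,000 runs). Trends of 0.3, 0.6 and 1.0 SD give 18%, 44% and 42%; the peak lies between the last two.

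**4. Mann-Whitney between arms.** Simulated power with 10 per arm, d = 0.64, two-sided α 0.05, normal data with equal SDs, one follow-up visit, 2,000 runs per setting:

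| ρ (assumed) | Mann-Whitney, raw | Mann-Whitney, change | Rank ANCOVA |
|---|---|---|---|
| 0.3 | 0.25 | 0.19 | 0.28 |
| 0.5 | 0.25 | 0.25 | 0.31 |
| 0.7 | 0.24 | 0.37 | 0.40 |
| 0.8 | 0.23 | 0.51 | 0.51 |

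With log-normal data the ranges over the same correlations are 0.23 to 0.25 (raw), 0.15 to 0.41 (change) and 0.26 to 0.51 (rank ANCOVA). Type I error was about 0.035 to 0.06 throughout.

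The pattern follows from the variances. With unit SD at both visits, the variance of a change is 2(1 − ρ), which is below 1 only when ρ > 0.5. Change scores therefore beat raw values only above about 0.5, whereas rank ANCOVA was ahead of raw values at every correlation tried.

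The 0.81 in step 1 and the 0.23 to 0.25 here rest on different effect definitions. Their difference is not a like-for-like loss of power.

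**The case against.** A reader might infer that the fallback ignores baseline and leaves the treatment effect on change untested. The article does not support that. It is silent on the Mann-Whitney variable, and because the primary outcome is itself a change, the test may well be meant for change scores; it would then test the arm difference in change. Even on raw follow-up values, randomization makes it a valid between-arm test, as the type I error shows. What remains is lower efficiency and exposure to chance baseline imbalance with 10 per arm.

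A reader might also call the normality switch a coin flip. The figures of about 25% in step 2 do not say that, and they depend on which values are tested. Nor does the article say that a treatment conclusion will be drawn from one arm's Friedman test; it labels those tests as intragroup. The switching rule is stated in advance, and the Masking/blinding section has the analyst blinded, which limits opportunistic choice.

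The efficiency loss can be made to look larger. With d = 1.27 and correlation 0.7, raw Mann-Whitney has 73% power against 92% for rank ANCOVA. But d = 1.27 is not in the article, and under the same inputs Mann-Whitney on change also reaches about 92%. At d = 0.64 and correlation 0.3 to 0.5, rank ANCOVA gains only about 3 to 6 points.

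Finally, a condensed article may leave the variable and visit of a fallback test to a fuller plan. That weakens a complaint about silence alone. It does not answer the stated defect: the article itself fixes a data-driven switch to a pair of tests that has no counterpart to the group-by-time term.

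**Conclusion.** The point holds in this form: the primary comparison is selected by a weak test on about 10 values per arm, and the alternative it selects does not clearly answer the same question. Friedman/Dunn cannot carry a treatment conclusion. The Mann-Whitney test can, but what it compares is left open.

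If it is run on raw follow-up values at the article's own d of 0.64, it has about 0.23 to 0.25 power, and rank ANCOVA on baseline has 0.28 to 0.51 over correlations 0.3 to 0.8. The gain is small at low correlation and about double at 0.8.

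These sizes rest on assumptions that the article does not give: the correlation between visits, two-sided testing, equal SDs (the cited SDs differ nearly threefold, 11.96/4.23 = 2.8), the distribution shapes, and AUC as the glucose measure. The structural point needs none of them. This should be corrected before analysis; it does not make the planned between-arm test invalid.

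**What to change.** 1. Drop Shapiro-Wilk as the switch. Inspect model residuals instead.
2. State one primary between-arm comparison that holds whatever the distribution: the chosen OGTT measure at a named visit (for example week 9), adjusted for its baseline value and for the puberty stratum used in randomization. A log scale can be specified in advance if the measure is expected to be right-skewed.
3. Name one robust check of the same comparison: rank ANCOVA on baseline, or a permutation test of the adjusted arm effect.
4. If Mann-Whitney is kept as a supporting analysis, state its variable and visit.
5. Label Friedman/Dunn results as descriptive, with no treatment conclusion drawn from them.

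The cost is analysis wording, a few lines of code, and one or two degrees of freedom for baseline and stratum. With 20 participants, intercept, arm, baseline and stratum leave 20 − 4 = 16 residual degrees of freedom. No change to data collection or sample size is needed for this point.

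### One set of effect-size bands, suited to a standardised mean difference, is applied to Cohen's f, Kendall's W and r: two-group effects are labelled too low on f and r, and the labels for W have no basis

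*Protocol article*

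**What the plan says.** In the protocol article, Statistical analysis, numerical outcomes go to a two-way mixed ANOVA, and "The effect size (ES) will be analyzed using" Cohen's f. If the data are not normal, the Friedman test is used within groups with Kendall's W, and the Mann-Whitney test between groups with r. One rule then covers all three indices: "Each ES will interpreted on the basis of Cohen as follows", followed by small 0.21–0.49, medium 0.50–0.79 and large 0.80 or more. No index has its own scale, and no standardised mean difference is planned.

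The Sample size calculation section bears on the scale in use. It plans "with an effect size of 0.30", without naming the index, and concludes that "the sample size calculation was 20 participants, with 10 in each group". The abstract's Methods give three visits: "All outcomes will be assessed at baseline, week 9, and week 17".

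**The concern.** The indices f, W and r are not on the same scale as d, or as one another. A label that fits a given value of d does not fit the same value of f or r. If the rule is followed as written, a between-group effect that is large as a standardised mean difference can be reported as small or medium. The same effect can also receive different labels depending on whether its outcome went to the ANOVA or to the rank tests. In a trial of 20 children, where estimates will be imprecise, readers may give the verbal labels some weight. What is at stake is the wording of the results, not any decision rule.

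**Working it through.** **Inputs.** Bands and indices: Statistical analysis. Planning means and SDs 34.47 ± 4.23 and 40.20 ± 11.96, effect size 0.30, N = 20, α = 0.05, power 80%: Sample size calculation. Three visits: abstract. Assumptions: the bands are read as d bands (the cited source is not at hand), and r is taken as Z/√N.

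**1. The plan's own figure.** For a repeated-measures ANOVA interaction with 2 groups and m = 3 visits, λ = f²·N·m/(1 − ρ). With f = 0.30 and assumed ρ = 0.5 and full sphericity, λ = 0.09 × 20 × 3/0.5 = 10.8 on 2 and 36 df. Power is 0.812, and N = 20 is reproduced. Read as d, 0.30 would need 176 per arm in a two-sided t test. The quoted means give a pooled SD of √((4.23² + 11.96²)/2) = 8.97, so d = 5.73/8.97 = 0.64 and f = 0.32. The planning figure is therefore on the f scale.

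**2. Two-group contrast.** With equal groups, f = d/2 and r = d/√(d² + 4). Labels by the plan's bands:

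| d | f | r | label as d | label as f | label as r |
|---|---|---|---|---|---|
| 0.50 | 0.25 | 0.24 | medium | small | small |
| 0.80 | 0.40 | 0.37 | large | small | small |
| 1.00 | 0.50 | 0.45 | large | medium | small |
| 1.60 | 0.80 | 0.62 | large | large | medium |
| 2.67 | 1.33 | 0.80 | large | large | large |

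The third and fourth rows show f and r disagreeing with each other. That conflict does not depend on reading the bands as d bands.

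**3. Mann-Whitney r with 10 per arm.** The SD of U is √(10 × 10 × 21/12) = 13.23.
- Complete separation (U = 0) gives Z = 50/13.23 = 3.78 and r = 3.78/√20 = 0.845, the maximum without ties.
- Large (r ≥ 0.80) needs Z ≥ 0.80 × 4.472 = 3.58, so 50 − U ≥ 47.3. That is U of at most 2 out of 100 pairs.
- The weakest result significant at two-sided 0.05 is U = 23 (exact P = 0.043): Z = 27/13.23 = 2.04 and r = 0.46, labelled small.
- The conversion in step 2 is close for this r. For normal data with d = 0.80, the chance that a member of one group exceeds one of the other is Φ(0.80/√2) = 0.714. This gives r of about 21.4/13.23/4.472 = 0.36, against 0.37.

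**4. Group-by-time interaction.** Here f = d/2 does not carry over. If f is taken from partial eta-squared, it equals √(λ/36) at the planning effect, with λ = 5.4/(1 − ρ):
- ρ = 0.3: λ = 7.71, f = 0.46 (small)
- ρ = 0.5: λ = 10.8, f = 0.55 (medium)
- ρ = 0.7: λ = 18.0, f = 0.71 (medium)

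**5. Kendall's W.** W is a 0-to-1 measure of concordance across visits within a group. It has no fixed conversion to d, so no size can be put on the mislabelling.

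**The case against.** Four points on the other side deserve weight.

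- *The planned parametric analysis is a mixed ANOVA, not a two-group contrast.* This stands. A reader might infer that the effect the trial was sized on would itself be labelled small. The article does not support that. It names neither the f convention nor a correlation between visits, and the label changes between small and medium across the range in step 4.
- *Not every medium or large effect becomes small.* This also stands. Values of f or r from 0.50 to 0.79 are labelled medium, and high enough values are labelled large. It would be too strong to say that all such effects are reported as small.
- *W is not offered as the treatment effect.* Correct. The article assigns W to the within-group Friedman analysis and r to the between-group comparison. The objection to W is only that these bands have no basis for it.
- *Nothing is decided by the labels.* Correct. Inference is by P < 0.05 and 95% confidence intervals, and understated labels would work against claiming a benefit. This limits the severity but does not make the rule right.

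Switching to f bands of 0.10/0.25/0.40 also has a cost in so small a trial. With no true effect and f taken from partial eta-squared on 2 and 36 df, the chance that f reaches a value c is (1 + c²)^(−18). This is 0.84 for c = 0.10 and 0.34 for c = 0.25. Any verbal label on a point estimate is fragile here, which favours intervals over labels.

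**Conclusion.** The point holds and is minor. One scale cannot serve f, W and r, and the scale given suits an index that the plan does not report. For two-group contrasts the labels run low: d = 0.80 is called small on both f and r, f or r of 0.50 to 0.79 (d of 1.0 or more) is called medium, and large on r needs near-complete separation with 10 per arm.

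These sizes rest on equal groups, on reading the bands as d bands, and on r = Z/√N. For the interaction f, neither the direction nor the size of the error can be fixed without the f convention and the correlation between visits. For W it cannot be quantified at all. The tests, P values and sample size are unaffected.

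**What to change.** Either of two edits to Statistical analysis would do.

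1. Drop the verbal labels and report each effect size with its 95% confidence interval. This is the simpler choice at N = 20.
2. Keep labels, but state them by index. For f, use 0.10/0.25/0.40 and name the convention by which f is computed. For r, state its own scale, for example the d-equivalent 0.10/0.24/0.37. Give no verbal label for W. Keep 0.2/0.5/0.8 only for a standardised mean difference, if one is reported.

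The cost is a sentence or two of text, with no effect on data collection, participants or planned tests. It is best made before results are seen by arm.
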